### 3.3.4 Follow-up visit prior to discharge

A follow-up visit will be conducted the day prior to discharge or the day of discharge. Information on the discharge location (home, nursing home, rehabilitation, other hospital), and the date of discharge (in order to assess length of hospital stay) will be obtained from medical records and/or interview of the participant and treating health care personnel (**Table 5**). In addition, potential medical outcome events will be assessed (see section 2.2). Autonomy will be assessed in a face-to-face interview using the modified Barthel Index (see sections 2.2.3 and 3.3.3.1).

Similar to the baseline visit, information on treatments since admission with a focus on pharmacological and mechanical TPX will be assessed in order to determine duration of TPX (**Table 5**).

Study personnel will collect the accelerometer and upload accelerometry data to the database using the relevant software (Geneactiv and R).

In case a patient dies during the hospitalization, study nurses will collect the accelerometer on the day of death. Also, information on the circumstances of death from medical records and interview of the treating physicians will be collected.

**Table 5. Data collection at discharge**

|                                                                                                                                                                                                                                                                                                                                                                  |
|------------------------------------------------------------------------------------------------------------------------------------------------------------------------------------------------------------------------------------------------------------------------------------------------------------------------------------------------------------------|
| Discharge information                                                                                                                                                                                                                                                                                                                                     |
| Date of discharge, discharge location                                                                                                                                                                                                                                                                                                                            |
| Medical outcome events                                                                                                                                                                                                                                                                                                                                    |
| HA-VTE, all-cause death, major bleeding, clinically relevant non-major bleeding                                                                                                                                                                                                                                                                                  |
| Autonomy                                                                                                                                                                                                                                                                                                                                                  |
| Modified Barthel Index                                                                                                                                                                                                                                                                                                                                           |
| Treatments since admission                                                                                                                                                                                                                                                                                                                                |
| Pharmacological thromboprophylaxis: type (low molecular weight heparin, unfractionated heparin, fondaparinux, other), start date; mechanical VTE prophylaxis (lower extremity compression stockings/bandages, intermittent pneumatic compression devices); therapeutic anticoagulation, red blood cell transfusions (and date), central venous catheter, surgery |

### 3.3.5 Follow-up phone call 90 days after enrolment

A final follow-up call will be scheduled at day 90 (range day 85-95) after study inclusion. The follow-up phone call will be conducted by trained study personnel at the local study sites. Medical outcomes (HA-VTE, all-cause mortality, major bleeding and clinically relevant non-major bleeding), subsequent hospitalizations since discharge, autonomy in the activities of daily living will be assessed. Assessment of endpoints is described in section 2.2.3. As initiation of therapeutic anticoagulation during follow-up will affect the outcomes, we will also collect information on new treatments, i.e. therapeutic anticoagulation since discharge.

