## 2.2 Primary and secondary endpoints

### 2.2.1 Primary endpoint

The primary outcome will be symptomatic, objectively confirmed fatal and non-fatal HA-VTE, including symptomatic distal and proximal DVT and PE up to 90 days after hospital admission.

The objective diagnostic criteria for a PE diagnosis will be based on available radiographic or autopsy reports, and will include a new intraluminal filling defect on computed tomography pulmonary angiography (CTPA) or pulmonary angiography; a perfusion defect involving at least 75% of a segment, with corresponding normal ventilation (i.e., high probability lung scan); the confirmation of a new PE on autopsy, or an objectively confirmed proximal DVT with clinical signs and symptoms of PE. The objective diagnosis of DVT will be the non-compressibility of a venous segment on compression ultrasonography or an intraluminal filling defect on contrast venography. Because iliac veins and the inferior vena cava may be technically difficult to compress, additional diagnostic criteria for iliac and caval DVT will also include abnormal duplex flow patterns compatible with thrombosis or an intraluminal filling defect on spiral computed tomography or magnetic resonance imaging venography. We will consider both proximal and distal symptomatic DVTs. In line with previous studies on VTE prophylaxis and given similarities in some risk factors and outcomes, symptomatic upper extremity DVT will also be considered as a study outcome, although its incidence is expected to be low. VTE events diagnosed during the first 48 hours of hospitalization will not be considered as a primary outcome for this study in order to rule out pre-existing VTE that occurred prior to hospital admission.

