### 2.2.3 Assessment of endpoints

To obtain information on the occurrence and timing of outcome events, study personnel will conduct patient visits on the day prior or the day of discharge, and will contact patients, family members, and/or primary care physicians by phone at 90 days after admission.

Medical records will be collected and reviewed to obtain information about the date/type/circumstances of medical outcome events (HA-VTE, major and clinically relevant non-major bleeding, death). In patients who experienced HA-VTE, radiographic reports and images will be obtained. For patients who died, the cause of death based on medical reports, death certificates, and autopsy reports (if available) will be recorded.

Patient's autonomy in the activities of daily living will be assessed using the modified Barthel index in a face-to-face interview at hospital discharge, and by phone at 90 days after admission. The modified Barthel Index has been reported as being the most accurate scale to assess activities of daily living (ADL) and has thus been widely used as a measure of autonomy. The modified version improves the internal consistency and provides a better discrimination of functional ability compared to the original version. The patient's ability to perform different ADLs will be rated as follows: fully independent, with minimal or moderate help, attempts task but unsafe, and unable to perform. The maximum point score is 100; a total modified Barthel Index point score of 0-20 suggests total, 21-60 severe, 61-90 moderate, and 91-99 slight dependence. A point score of 100 indicates that the patient is independent of assistance from others.

To assess length of hospital stay, admission and discharge times/dates will be obtained from hospital charts. The number of subsequent hospitalizations up to 90 days after admission will be obtained through patient interview during the follow-up phone call, interview of the patient's primary care physician, or hospital chart review.

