## 2.3 Project design

We will conduct a multicenter national non-interventional prospective cohort study including consecutive consenting adult patients admitted to general internal medicine at ≥3 large-volume Swiss hospitals. VTE risk will be assessed at admission using the simplified Geneva score, and 3 other validated RAMs. Mobility will be measured during the hospitalization using accelerometry. Patients will be followed for the occurrence of HA-VTE, with a follow-up phone call at 3 months after admission (**Figure 3**).

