| Feasibility Substudy              |                                 |                      |                     |                                     |                  |
| Consent for hypothetical RCT                         |                                 |                      |                     | x                                   |                  |
| Medical Outcomes                              |                                 |                      |                     |                                     |                  |
| Symptomatic HA-VTE                                   |                                 |                      |                     | x                                   | x                |
| All-cause mortality                                  |                                 |                      |                     | x                                   | x                |
| Major bleeding                                       |                                 |                      |                     | x                                   | x                |
| Clinically relevant non-major bleeding               |                                 |                      |                     | x                                   | x                |
| Other study data                              |                                 |                      |                     |                                     |                  |
| Length of hospital stay                              |                                 |                      |                     | x                                   |                  |
| Discharge location                                   |                                 |                      |                     | x                                   |                  |
| Duration of VTE prophylaxis                          |                                 |                      |                     | x                                   |                  |
| Subsequent hospitalizations                          |                                 |                      |                     |                                     | x                |

 Enrolment and baseline visit may take place within 72 hours of admission

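### The only follow-up call may be made up to five days before the 90-day horizon of the primary endpoint, and the protocol counts its timing from two different dates

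*Protocol*

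**What the plan says.** **Counted from admission.** Protocol section 2.2.1 defines the primary outcome as "symptomatic, objectively confirmed fatal and non-fatal HA-VTE, including symptomatic distal and proximal DVT and PE up to 90 days after hospital admission". Section 2.2.3 says that study personnel "will contact patients, family members, and/or primary care physicians by phone at 90 days after admission", and section 2.3 describes the design "with a follow-up phone call at 3 months after admission". The secondary outcomes in section 2.2.2, including readmission, also run to 90 days after admission. Section 4.1.2 evaluates the accuracy of each score at 90 days.

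**Counted from inclusion.** Section 3.3.5 says "A final follow-up call will be scheduled at day 90 (range day 85-95) after study inclusion". Table 3 has the same window, with day 0 as the day of enrolment. Sections 3.3.1, 6.1 and 6.2 and the synopsis also count follow-up or the call from inclusion or enrolment.

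**The gap between the two dates.** A footnote to Table 3 says "Enrolment and baseline visit may take place within 72 hours of admission".

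**Other routes to the outcome.** Section 6.1 foresees a single telephone call and no on-site visit during follow-up. Section 2.2.3 provides for review of medical records to establish the date, type and circumstances of events. Section 3.5 requires a check of hospital records when a patient cannot be reached. Nothing says that records are searched through day 90 for a patient who was reached.

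**The concern.** A cumulative endpoint is observed in full only if the last contact comes on or after its horizon. Here a site can follow section 3.3.5 to the letter and close a patient on day 85 after admission, leaving days 86 to 90 unseen. An event in those days is missed unless records happen to reveal it. A patient without an event is censored before the time at which sensitivity and specificity are estimated.

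The primary analysis has methods for censoring, but readmission does not: section 4.1.2 analyses it by logistic regression, which treats a patient seen for 85 days like one seen for the full 90. Late calls can be repaired by discarding events dated after day 90. Days that were never observed cannot be recovered.

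The two anchors add a practical problem. Section 3.3.5 refers to section 2.2.3 for how endpoints are assessed, and section 2.2.3 uses the other date. Two sites could therefore run different schedules and both be compliant.

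**Working it through.** **1. The plan's own figure.** Inputs from section 4.1.1: 67% high risk and 33% low risk, 90-day incidence 2.8% and 0.6%, 80% power, two-sided alpha 0.05. With k = 33/67 and pooled incidence p = 0.67 × 0.028 + 0.33 × 0.006 = 0.02074,

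n(high) = [1.96 √((1 + 1/k) p(1 − p)) + 0.842 √(p1(1 − p1) + p2(1 − p2)/k)]² / (0.022)² = 882,

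n(low) = 435, total 1317. That is within 0.7% of the stated 1308, and power at 1308 is 79.7%. Expected events at 1308: 0.67 × 1308 × 0.028 + 0.33 × 1308 × 0.006 = 24.5 + 2.6 = 27.1.

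**2. When a compliant call can fall.** Day after admission = enrolment lag (0 to 3) + call day after inclusion (85 to 95), giving 85 to 98. The call is early if the sum is below 90: inclusion-days 85–89 at lag 0, 85–88 at lag 1, 85–87 at lag 2 and 85–86 at lag 3. A call on the day-90 target falls on days 90 to 93 after admission and is never early.

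**3. Share called early.** The protocol gives no distribution of call days, so these are assumptions. With an even spread over the 11 permitted days the shares are 5/11, 4/11, 3/11 and 2/11.

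| Assumed call days | Lag 0 | Lag 1 | Lag 2 | Lag 3 |
|---|---|---|---|---|
| Even over 85–95 | 45% | 36% | 27% | 18% |
| Triangular around 90 | 42% | 28% | 17% | 8% |
| Normal around 90, SD 2 days | 40% | 22% | 10% | 4% |
| All on day 90 | 0% | 0% | 0% | 0% |
| All on day 85 | 100% | 100% | 100% | 100% |

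Of 1350 patients, the even spread gives 614, 491, 368 and 245 early calls.

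**4. Events lost.** Assume a constant hazard over days 2 to 90 (88 days). Events lost = 27.1 × mean shortfall / 88.

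- Even spread, lag 0: mean shortfall (5 + 4 + 3 + 2 + 1)/11 = 1.36 days; 27.1 × 1.36/88 = 0.42.
- Normal spread, lag 3: mean shortfall 0.04 days; about 0.01.
- All on day 85, lag 0: 27.1 × 5/88 = 1.54, the upper limit.

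**5. Power.** Multiplying both incidences by (1 − mean shortfall/88) at N = 1308 takes power from 79.7% to 79.0% (even spread, lag 0), or to 76.9% (all on day 85, lag 0).

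**6. Specificity.** Controls: 1308 − 27.1 = 1280.9. The Wilson 95% interval at 34% is 31.5% to 36.6%. If only controls followed to day 90 counted (even spread, lag 0: 1280.9 × 6/11 = 699), it would be 30.6% to 37.6%.

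**7. Readmission.** No rate is given, so no count can be computed. The unobserved part is at most 5/90 = 5.6% of the period for any one patient.

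**8. With no call before day 90 after admission.** Early calls 0%, expected events 27.1, power 79.7%.

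**The case against.** The best defence is that the effect is slight and largely allowed for. The call is targeted at day 90, and calls made on target always reach the horizon. Enrolment on the day of admission, the worst case, may be uncommon: Table 3 as rendered places admission before day 0, section 3.2 gives patients up to 24 hours to decide, and weekend admissions are screened on the next working day. With lags 1 to 3 equally likely and calls spread evenly, the share is (4 + 3 + 2)/33 = 27%. The time-dependent ROC analysis is specified to allow for censoring and competing events, and records are a further source. All of this stands, and it limits the size. It does not remove the fault: a stated rule still permits contact to end before the primary endpoint does, and no stated step covers the remaining days for patients already reached.

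Three stronger readings are tempting and are not supported.

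- *Many patients will be censored early.* The documents do not show this. The share ranges from 0% to 100% with the call-day distribution, which is not given.
- *Counting from inclusion causes the shortfall.* It works the other way: inclusion is on or after admission, so that anchor makes calls 0 to 3 days later.
- *The start of the clock is mis-set, and about one event in 27 is lost at the front.* Section 4.1.2 states no time origin, so none is set wrongly. Section 2.2.1 says "VTE events diagnosed during the first 48 hours of hospitalization will not be considered as a primary outcome for this study", and entry is within 72 hours, so only hours 48 to 72 could be lost. That is at most one day, or 27.1/88 = 0.3 event, and only if everyone enrolled at hour 72. Delayed entry and the handling of VTE within 48 hours are matters that an analysis plan may settle.

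**Conclusion.** The point holds in a narrow form. The lower bound of the call window precedes the horizon of the primary endpoint by up to five days, and the protocol uses two anchors for the same call. The consequence is modest: under 0.5 of about 27 expected events under the three spreads, with an upper limit of about 1.5, and power between 76.9% and 79.7%. Specificity at day 90 is somewhat less precise if controls without full follow-up contribute nothing; a method that handles censoring would recover part of that. Readmission is the outcome with no such protection.

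These sizes rest on assumed call-day spreads, lags of 0 to 3 days, and a constant hazard from day 2 to day 90. If risk is concentrated earlier, fewer events fall in the last five days and the loss is smaller. The conclusion about the window needs none of these assumptions, because it follows from the stated dates. The change is worth making because it is cheap and secures full observation of the primary endpoint; the study is not invalid without it.

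**What to change.** 1. Use admission as the single anchor in sections 2.2.3, 3.3.1 and 3.3.5, Table 3 and the synopsis, and in sections 6.1 and 6.2, which repeat the inclusion anchor.
2. Make the call no earlier than day 90 after admission, for example days 90 to 97.
3. Have the caller ask about events through day 90 after admission, record their dates, and truncate all cumulative outcomes, including readmission, at day 90.
4. Leave the time origin, delayed entry and the handling of VTE within 48 hours to the statistical analysis plan.

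**Cost.** Protocol and Table 3 wording, and calls a few days later: the earliest permitted day moves from 85 to 90 after admission. The latest, day 97, is within the day 98 already possible (95 + 3). The example window has 8 days against 11 now. If that is too tight, it can be extended at the upper end, since truncation at day 90 keeps the observation period equal. The Barthel Index, a status at one time point, would be taken up to a week after its nominal day, which is a minor drawback. No contact is added and the sample size is unchanged.

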## 3.4 Risks and measures to minimize the risks

Ideally, we would conduct this study in medical inpatients who do not receive any TPX, which is ethically not feasible. Thus, a substantial proportion of patients (<60%) will receive TPX, which may decrease VTE risk and by consequence incidence of HA-VTE. However, as no RAM is formally implemented in the participating hospitals, we expect that patients with and without TPX will be well distributed in low and high VTE risk groups. Also, we will adjust our analyses for

receipt of TPX and conduct sensitivity analyses excluding patients with TPX. Given the non-invasive nature of accelerometry and its good acceptability among inpatients based on the literature and on PI's practical experience, we do not expect its implementation to cause any problems. Due to the observational design of our study, we do not expect safety issues for the patients enrolled.

### **3.5 Withdrawal and discontinuation**

Participants can leave the study at any time for any reason if they wish to do so without any consequences. Investigators will make every reasonable effort to keep each patient on the study until all planned assessments have been performed. Protocol violations will not lead to patient withdrawal from the study.

Withdrawals were accounted for in our sample size calculation (see section 4.1.1); therefore, participants who withdraw from the study after provision of informed consent will not be replaced.

For a patient who withdraws consent for accelerometry-based measurements or for follow-up prior to hospital discharge, the option of an assessment at 90 days will be provided. Whether a withdrawing patient agrees or refuses to have the final 90 day assessment performed, this will be noted in the CRF.

If a study withdrawal occurs, coded data collected up to the time of withdrawal may nevertheless be used, as stipulated by the Swiss Human Research Ordinance (HRO Art. 10); we will inform potential participants in the patient information that anonymization is not possible, as done previously. In addition, patients withdrawing consent for further study participation will be asked whether he/she would nevertheless agree with follow-up information being collected based on available hospital records and/or follow-up with his/her primary care physician, and the patients' decision will be noted in the CRF.

If a participant is lost to follow-up (i.e. a participant whose status is unclear because he/she cannot be reached for the follow-up phone call), the primary care physician and/or surrogate (relative or close friend) that were indicated by the participant during the baseline visit will be contacted and the hospital electronic records will be verified to obtain information about recurrent VTE and vital status. The steps taken to contact the participant, his/her primary care physician, and surrogates (i.e. dates of phone calls) will be noted in the CRF.

